## Abstract

**Introduction:**

Sarcopenia is a chronic and progressive disease, which is accompanied by the decline in muscle mass, muscle strength, and physical performance with aging, and it can lead to falls, fracture, and premature death. The prevention and treatment of sarcopenia mainly include exercise therapy and nutritional supplement. Exercise therapy is one of the most potential interventions to prevent and/or delay the progression of sarcopenia. Resistance training (RT), one of the most commonly used exercise types, is widely used in the treatment of sarcopenia, while vibration training (VT) is a prospective strategy for improving sarcopenia in older people. The aim of our study is to compare the effect of VT and RT in older people with sarcopenia on muscle mass, muscle strength, physical performance, blood biomarkers, and quality of life.

**Methods and analysis:**

Our study is a 12-week, three-arm randomized controlled trial with assessor-blinded. The diagnosis criteria for subject recruitment adopt the guidelines for the Asian Working Group for Sarcopenia. A total of 54 subjects who met the criteria were randomized into one of the following three groups: VT group, RT group, and control group. The VT group and RT group received a 12-week whole-body vibration training and a resistance training program three times every week, respectively. The primary outcome is lower limb muscle strength, and the secondary outcomes include muscle mass, upper limb muscle strength, physical performance, blood biomarkers, and quality of life. We then performed assessments three times, at baseline (0 week), after intervention (12 weeks), and follow-up (24 weeks). The adverse events were also be reported. All outcome measurements were performed by the same researchers. Data were saved in the unified database, and the collected data of all subjects were analyzed by intention-to-treat analysis.

**Ethics and dissemination:**

This study was reviewed and approved by the Ethical Committee of Xinhua Hospital Chongming Branch. The findings of the study were authorized in peer-reviewed journals with online access; meanwhile, it will be presented at domestic or international academic congresses.

**Clinical trial registration:**

Chinese Clinical Trial Registry (ChiCTR2100051178), registered on 15 September 2021.

## Introduction

Sarcopenia is a progressive disease associated with aging, characterized by low skeletal muscle mass, decreased muscle strength, and/or poor physical performance (Chen et al., 2020). In China, the prevalence of sarcopenia in older people aged 60 years and above in the suburb-dwelling population was 9.3%, with 6.4% in men and 11.5% in women according to the guideline for the Asian Working Group for Sarcopenia (AWGS) (Han et al., 2016). Several adverse outcomes, such as accidental falls (Zhang et al., 2020), fractures of upper and lower limbs (Zhang et al., 2018), physical disability (Janssen et al., 2002), cognitive impairment (Peng et al., 2020), poor quality of life (Tsekoura et al., 2017), or even death (Nascimento et al., 2019), are associated with the progression of sarcopenia. The changes of older people with sarcopenia are not only reflected in clinical outcomes (Chen et al., 2020) and physiological outcomes, such as age-related inflammation (Tournadre et al., 2019), metabolic abnormalities (Hunter et al., 2019), and endocrine changes (McKee et al., 2017). The pathophysiological mechanisms of sarcopenia are complexly associated with the following blood biomarkers: inflammatory factors {i.e., hypersensitive C-reactive protein [hs-CRP] (Shokri-Mashhadi et al., 2021), tumor necrosis factor-α cytokines [TNF-α] (Bian et al., 2017), and interleukin-6 [IL-6] (Rong et al., 2018)}, hormones {i.e., insulin growth factor-1 [IGF-1] (Ascenzi et al., 2019), growth hormone [GH] (Bian et al., 2020), testosterone (Colla et al., 2015), and 25(OH)D (Remelli et al., 2019; Abiri and Vafa, 2020)}, growth factors {i.e., myostatin [MSTN] (White and LeBrasseur, 2014) and follistatin [FST] (Echeverria et al., 2021)}, and muscular injury biomarkers such as creatine kinase (CK) (Kurita et al., 2021). The adverse outcomes of sarcopenia inflict a huge economic burden to patients and their families (Bruyère et al., 2019). Therefore, some measures should be taken to prevent and/or delay the development of the sarcopenia.

Until now, there is no particularly effective pharmacological treatment for sarcopenia (Cruz-Jentoft and Sayer, 2019), and many studies have indicated that non-pharmacological treatment is the most potential treatment, especially exercise training, and results in significant improvements in muscle function and physical fitness in older people with sarcopenia (Lo et al., 2020). Currently, one of the most commonly used exercise trainings for older people with sarcopenia is resistance training (RT) (Beckwée et al., 2019). Vibration training (VT), a prospective strategy for improving sarcopenia in older people (Wu et al., 2020), is a training method that uses the vibration platform with different vibration frequencies and amplitudes in different positions (Nordlund and Thorstensson, 2010). In recent years, the application of VT has been more widely used to delay the loss of muscle functions in older people with sarcopenia (Wei and Ng, 2018; Camacho-Cardenosa et al., 2019; Zhu et al., 2019). A meta-analysis demonstrated that VT can change the declining trend of muscle mass, muscle strength, and physical performance (Wu et al., 2020); meanwhile, several studies have confirmed that VT has positive effects on sarcopenia (Wei et al., 2016, 2017; Chang et al., 2018; Wei and Ng, 2018). Thus, VT may be a potential alternative training method to improve sarcopenia compared with conventional resistance training (CRT), which is generally a high-intensity RT. Although a large number of studies have confirmed the benefits of VT on muscle function, there is still a lack of comparison of the effects between VT and CRT in older people with sarcopenia. For VT to replace CRT, it is necessary to compare the effects of the two training methods on sarcopenia in older people.

RT is the most effective method to improve muscle function and physical performance in older people. The American College of Sports Medicine (ACSM) (Nelson et al., 2007) and the World Health Organization (World Health Organization, 2018) recommend 2–3 times of RT (60–80% of one repetition maximum [1RM]) per week. The intensity of RT recommended by the ACSM is ≥ 70% 1RM to achieve significant muscle hypertrophy among older people (American College of Sports Medicine, 2009). Similarly, it is demonstrated that high-intensity RT (60–70% 1RM) can produce significant effects on muscle conditions and physical performance in older people (Chen et al., 2017; Guizelini et al., 2018; Sahin et al., 2018) compared to low-intensity RT (40% 1RM) (Lixandrão et al., 2017; Sahin et al., 2018). However, RT needs high-technology requirements for older people (Wernbom et al., 2008; Thiebaud et al., 2014) and it is easy to produce muscle fatigue (Jacko et al., 2018). These may reduce the compliance of older people, especially for frail older people, and are difficult to generally conduct in the clinical setting.

Thus, the aims of our study are to (1) evaluate the effects of 12-week VT and RT on muscle mass, muscle strength, physical performance, blood biomarkers, and quality of life in older people with sarcopenia; (2) compare the effects of VT and RT on sarcopenia; and (3) explore the mechanisms of VT and RT on the improvement of sarcopenia.

## Methods and analysis

### Study design

This study is a three-arm, assessor-blinded, randomized control trial. The experimental flowchart is given in Figure 1. The schedule of enrollment, interventions, and assessments for our study is shown in Table 1.

**Figure 1 F1:**
[figure not shown]
Experimental flowchart showing the patient recruitment, intervention, and assessment process.

**Table 1 T1:** Schedule of enrollment, interventions, and assessments.

**Study period**
**Timepoint**		**Before week 0**	**Week 0**	**Week 1–12**	**Week 12**	**Week 24**
Screening	Eligibility screening	X				
Allocation	Informed consent	X				
Intervention	VT			X		
	RT			X		
	Education (No intervention)			X		
Assessment	Muscle mass		X		X	X
	Muscle strength		X		X	X
	Physical performance		X		X	X
	Blood biomarkers		X		X	X
	Quality of life		X		X	X
Others	Subjects' compliance		X	X	X	X
	Adverse events		X	X	X	X
	Dropout reasons			X		

VT, vibration training; RT, resistance training.

### Study setting

We selected subjects for our study from four communities in Chongming district of Shanghai, China, who met the inclusion and exclusion criteria. This study was conducted in May 2022 at Xinhua Hospital Chongming Branch. A total of 54 older people met the eligibility criteria and were enrolled in the study. The subjects were stratified by sex and then randomized into one of three groups (18 in each group): VT group, RT group, and control group. The assessments were performed three times: at baseline (0 week), after intervention (12 weeks), and follow-up (24 weeks).

### Inclusion criteria

People aged between 65 and 80 years;Older people diagnosed with sarcopenia according to the criteria for AWGS: appendicular skeletal muscle mass index (ASMI) < 7.0 kg/m^2^ for male (M) and < 5.7 kg/m^2^ for female (F) using a bioelectrical impedance analyzer (BIA); handgrip strength (HGS), M: < 28 kg, F: <18 kg; and/or gait speed (GS) < 1.0 m/s in the 6-m walk (6-MW) test;The participants without serious diseases, such as uncontrolled hypertension, hyperlipidemia, hyperglycemia, and diabetes;The participants without untreated diseases, such as gallstones or kidney stones, and infectious diseases;The participants with no regular exercise habit for more than 3 months.

### Exclusion criteria

People with absolute contraindication for exercising, such as deep venous thrombosis and/or blood clotting disorders;People with serious cognitive impairments that have impact on the assessments and communication with researchers, such as dementia and mental illness;Individuals suffering from serious diseases that affect the assessments and interventions, such as musculoskeletal diseases (e.g., fracture, dislocation, osteoporosis, and rheumatoid arthritis) and disability (e.g., loss of hands, feet, or limbs);Individuals with serious spinal diseases or a surgical history, such as vertebral fracture, inflammatory joint disease, ankylosing spondylitis, spondylolisthesis, rheumatism, cauda equina syndrome, and tumor;Individuals who have taken the following drugs regularly in past 3 months: antiplatelet agents (e.g., aspirin, Aggrenox, cilostazol, eptifibatide, ticlopidine, and tirofiban), anticoagulant drugs, and analgesic drugs;Patients with other diseases whose participation in this study is not recommended by doctors;Patients who did not sign the informed consent before the beginning of study.

### Termination criteria

The participants having serious adverse events or complications during the intervention period and cannot continue to participate in the study;The participants who proposed that they were unwilling to continue to participate in the study;Lost contact with subjects during the experiment and/or follow-up.

### Recruitment

The subjects were recruited using three approaches: (1) the annual community physical examination in four communities in Chongming district; (2) educational lectures and talks about sarcopenia at community centers; (3) home visits in cooperation with workers in the community, and the physical examination of older people who do not participate in community activities regularly for a long time.

### Screening

The subjects were screened by a screening questionnaire called SARC-F, which assesses five aspects in older people: strength, assistance in walking, rising from a chair, climbing stairs, and falls (Malmstrom and Morley, 2013; Malmstrom et al., 2016). The SARC-F questionnaire has a score range (0 [best] to 10 [worst]) for the initial diagnosis of sarcopenia, and older people with scores ≥ 4 points were considered as having a risk of sarcopenia (Chen et al., 2020). Then, the older people with a score ≥ 4 points underwent a further screening in accordance with the AWGS standard: (1) the assessment of HGS using a hand dynamometer (Jamar Plus+ Digital Hand Dynamometer; IL, USA), M: < 28 kg, F: < 18 kg; or (2) and five-time chair stand (5-CS) test, the time of the 5-CS test ≥ 12 s. If the results of the measurements meet the aforementioned standards, older people were considered “possible sarcopenia”. A formal assessment of sarcopenia was performed using the ASMI with a portable BIA system (Inbody, S10, Korean), M: < 7.0 kg/m^2^, F: < 5.7 kg/m^2^, and the assessment of the 6-MW test, the result of GS < 1.0 m/s.

### Randomization and blinding

The subjects were informed of the purpose of the study and the safety risks that may happen in the study, and if they were willing to participate in the study, informed consent was required to sign before the subjects were screened. A stratified randomization method by sex was performed on the subjects meeting the eligibility criteria for a balanced distribution so that each group will have the same number of males and females. The stratified randomization sampling was performed by a researcher, who did not participate in our experiment, by a computer program (Research Randomizer Form www.randomizer.org). The subjects were then randomized into three groups: VT group, RT group, or control group at a 1:1:1 ratio. The randomized number and group assignments were sent to a researcher, who also did not participate in our study, as an electronic file with encryption to store the experimental information. The therapists for different intervention groups conducted the intervention according to the group assignments. Only the therapists will not be blinded to the group assignments, and other research staff (including the assessors, data managers, and data statisticians) will be blinded to the group assignments.

### Interventions

#### Group protocols

A pre-training for the VT group and RT group were performed three times to familiarize them with the corresponding training courses. Formal training was conducted after pre-training. In two intervention groups (VT ang RT groups), 5-min warm-up and cool-down training were conducted before and after intervention. All training sessions were carried out by physical therapists. During the whole training period, the researchers recorded the participants' attendance and compliance. If a subject could not participate in the training on time due to some reasons, training was performed at other times in that week. All subjects were asked not to perform additional physical activity and/or change their daily lifestyle during the experimental period.

#### Vibration training program

The VT group received a 30-min whole-body vibration training (WBVT) three times a week for 12 weeks. For the WBVT, a vibration platform generating vertical vibrations (Siehe Typenschild, Wellengang excellence, Germany) was used. Each training lasted about 30 min, which included a 5-min warm-up, 20-min vibration training, and 5-min cool-down. The vibration frequency was progressively increased to 20–25 Hz and the peak-to-peak amplitude of 4 mm. During the WBVT, the subjects was asked to stand barefoot on the vibration platform with knees flexion at 30°, and a vibration rope, if needed, were held by the subjects with both hands to maintain balance. And the movement in WBVT should maintain 1 min, and repeat 10 groups with 1-min resting between groups in each training day.

#### Resistance training program

The RT group received a 12-week resistance exercise program for three times every week. Each exercise session included three parts: (1) a 5-min warm-up (mainly stretching) of the neck, shoulders, lower back, hips, knees, and ankles; (2) a resistance exercise training, which consisted of three sets/10 reps of each exercise session, and the subjects had a 1-min rest between sets. The TheraBand elastic band is used for the resistance exercise training. Before beginning the intervention, each subject should complete the 1RM test to evaluate muscle strength and determine the intensity of resistance exercise training. According to the results of the 1RM test, the intensity of resistance exercise training was specified according to the individual's 1RM. The intensity was 60% 1RM in the first 4 weeks, 65% 1RM in the second 4 weeks, and 70% 1RM in the third 4 weeks. Resistance exercise movements include upper limb exercises (elbow flexion, shoulder extension, and abduction), lower limb exercises (hip abduction, knee flexion, and extension), and trunk exercises (chest press); and (3) a 5-min cool-down was performed after the aforementioned exercise training, which is similar to the warm-up exercise.

#### Control group with education courses

The subjects in the control group received a 60-min education course two times a month at the community center. The education course was taught by the invited experts, and the topics of courses were aging, health, and sarcopenia, including the definition of sarcopenia, cause of disease, pathology, clinical performance, and adverse consequences for older people.

#### Nutritional intake control

During a 12-week intervention period and a 12-week follow-up period, all subjects were required to maintain their dietary habits. The study staff and community workers supervised and recorded the nutritional intakes, and the record content on the specific notebook includes the diet of three meals a day for protein, fat, etc. The frequency of dietary recording should be maintained at two times a week on weekdays and once on weekends.

### Outcome measurements

The outcome was measured at baseline (0 week), after invention (12 weeks), and follow-up (24 weeks).

#### Primary outcome

Lower limb muscle strength was assessed by an estimated 1RM of knee extension strength (KES) (Abdalla et al., 2020). The 1RM test was the most popular method used for measuring muscular strength, but the standard 1RM test was too difficult for frail older people with sarcopenia and can even cause the injury to subjects (Rontu et al., 2010); therefore, our study chose the estimated 1RM test, which is more suitable to assess muscle strength for frail older people. The calculation is as follows: Estimated 1RM (kg) = submaximal weight (kg)/(1.0278–0.0278×maximal number of repetitions) (Brzycki, 1993). The subjects should sit on the extensor chair and the weight plates of extensor chair are in kilograms (Brzycki, 1993). In the beginning, the weight was set at M: 64% of the body mass and F: 45% of the body mass (Kuramoto and Payne, 1995; Abdalla et al., 2020). If a subject can perform knee extension 10 times under the initial weight, the weight was increased, and the repetitions of the maximal weight was recorded. Conversely, if the subject repeated 10 times or less, the weight was considered the submaximal weight. The maximal number of repetitions performed and the submaximal weight were used to calculate the estimated 1RM.

#### Secondary outcomes

##### Anthropometric measurements

Body height (BH) and body weight (BW) were measured by researchers. BH measurement requires the subjects to stand barefoot on the floor with the standard posture for measuring height. When measuring BW, the subjects were required to wear minimal clothes and stand barefoot on the digital weight scale. In addition, the calf circumference (CC) or other basic physical indicators of the subjects were measured and recorded.

##### Muscle mass

Muscle mass includes skeletal muscle mass (SMM), skeletal muscle mass index (SMI), appendicular skeletal muscle mass (ASM), and ASMI. These indicators were measured using the BIA (Inbody, S10, Korean). The SMI and ASMI were calculated (SMI= SMM/height^2^, kg/m^2^; ASMI= ASM/height^2^, kg/m^2^).

##### Upper limb muscle strength

HGS as an indicator of upper limb muscle strength was assessed by a Jamar^®^ hand dynamometer (Jamar Plus+ Digital Hand Dynamometer; IL, USA). The measurement process is as follows: in a standing position, the subjects were instructed to hold a dynamometer with the upper limb abducted at 30° from the body. The maximum HGS of each hand was measured and recorded continuously for three times, and the maximum value was considered as the final HGS value.

##### Physical performance

Physical performance was assessed using the Short Physical Performance Battery (SPPB) test, 6-MW test, and the Timed Up and Go (TUG) test.

The SPPB test includes a progressive standing balance test, a walk test, and a chair sit-to-stand test (Welch et al., 2020). In the balance test, the subjects were asked to stand in a side-by-side, semitandem and full-tandem positions, respectively. The subjects must stand at each position for at least 10 s. In the walk test, the subjects were asked to take a 4-m usual walk at the preferred GS from the standing position, and the tests were repeated two times, and the fastest time was selected. In the chair sit-to-stand test, the subjects were asked to fold their arms across the chest (without using one's arms) and try to complete five-time chair sit-to-stand tests as rapidly as possible.

Using the 6-MW test to assess GS, the subjects must walk 6 m at their usual speed. The test was repeated two times with the 2- to 3-min resting time, and the average value was calculated as the final GS.

The procedure of the TUG test is as follows: the subject should initially sit in the chair, stand up from the armchair (with the arms crossing in front of the chest), walk ahead 3 meters (at normal speed and as fast as possible), bypass the obstacle, walk back, and then sit down again (Podsiadlo and Richardson, 1991). The test was performed two times with a 2- to 3-min resting time, and the mean value was recorded as the final record.

##### Blood biomarkers

For each participant, the fasting venous blood sample after 12-h overnight fasting was collected by nurses in the morning about 08:00 for baseline (0 week), after intervention (12 weeks), and follow-up (24 weeks). The blood sample was sent to the laboratory for an automatic enzyme-linked immunosorbent assay to determine the level of blood biomarkers. The blood biomarkers include inflammatory factors (hs-CRP, TNF-α, and IL-6), hormones [IGF-1, GH, testosterone, and 25(OH)D], growth factor (MSTN and FST), and a muscular injury biomarker (CK).

### Quality of life

Quality of life in older people was assessed using the validated Chinese version of the 36-item Short-Form Health Survey (SF-36). The SF-36 consists of 36 items and eight health scales (physical functioning, role-physical, bodily pain, general health, vitality, social functioning, role-emotional, mental health, and reported health transition) assessing function and wellbeing of older people. The total score ranges from 0 to 100, and a higher score represents better quality of life.

### Sample size

In our study, we used G-Power software version 3.1 to calculated the simple size. A previous study showed that lower limb muscle strength can directly reflect the effect of exercise training on sarcopenia (Eckardt, 2016; Floreani et al., 2018). Thus, lower limb muscle strength was used as the primary outcome for the calculation of simple size. A power of 0.80 with an alpha of 0.05 was obtained in the calculation of simple size of each group, and the effect size was 0.48, which was reported in a previous meta-analysis study (Rogan et al., 2015). Our study adopted this effect size for calculating the sample size. We used above parameters in G-Power software and produced the total simple size as 45 subjects (15 subjects per group). Considering that there is a potential 20% drop rate of subjects, the total sample size should be 54 subjects (18 per group) in our study.

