### Statistical analysis

The results in the study took the questionnaire result and five components of the outcome measurements into account. All results were analyzed by IBM SPSS Statistics version 24 (SPSS, Inc., USA) with a statistical significant difference as *p* < 0.05. Continuous variables were represented by mean ± standard deviation or median. The chi-square test was used for categorical variables. For baseline characteristics data of between-group comparisons, we used the one-way analysis of variance (for parametric continuous data) or Kruskal–Wallis tests (for non-parametric continuous data).

The linear mixed model was used to analyze the differences in the outcome variables between the three intervention groups, which change over time following the principle of intention-to-treat. Missing data were assumed at random and then were processed by using the linear mixed model and maximum likelihood method.

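### The stated 80% power rests on an effect size of 0.48 with no stated metric or contrast; 45 subjects follow if 0.48 is Cohen's f in an omnibus ANOVA, not if it is a standardised mean difference

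*Protocol article*

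**What the plan says.** The calculation is in the Sample size section of the protocol article. The software is given as "we used G-Power software version 3.1", and the error rates as "A power of 0.80 with an alpha of 0.05 was obtained in the calculation of simple size of each group". The assumed effect is introduced with "the effect size was 0.48, which was reported in a previous meta-analysis study". The result reads "We used above parameters in G-Power software and produced the total simple size as 45 subjects (15 subjects per group", and is then raised to 54 (18 per group) for 20% dropout. The section names no G*Power test, no metric for 0.48, no contrast that 0.48 describes and no conversion.

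Two other places bear on this. The second aim, at the end of the Introduction, is to "compare the effects of VT and RT on sarcopenia". The Statistical analysis section says: "The linear mixed model was used to analyze the differences in the outcome variables between the three intervention groups, which change over time". Outcomes are measured at weeks 0, 12 and 24.

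**The concern.** A meta-analysis of continuous outcomes commonly pools two-group differences, whereas Cohen's f describes the spread of several group means. The two scales are not interchangeable. In three groups, a largest difference of d SD corresponds to an f of only about 0.41d to 0.47d. If a pooled difference was entered as f without conversion, the calculation assumed an effect more than twice the cited one.

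A second question is what the 80% refers to. An omnibus test can reject because either active arm differs from control. It gives no assurance about VT against RT, yet the Introduction says that this comparison is needed before vibration training could replace conventional resistance training.

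At stake is how a null result is read. A reader who trusts the stated 0.80 may take a non-significant VT–RT difference as evidence that the two are alike.

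**Working it through.** **Inputs from the protocol article:** alpha 0.05, power 0.80, effect size 0.48, 45 evaluable (15 per group) and 54 enrolled (18 per group) from Sample size; 1:1:1 allocation from Randomization and blinding. Pairwise tests are taken as two-sided (assumption). No baseline correlation is given, so a range is used.

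**1. Reproducing 45.** For a one-way ANOVA with k = 3, λ = N·f² with 2 and N − 3 degrees of freedom.
- f = 0.48, N = 45: λ = 45 × 0.2304 = 10.368, power 0.8005.
- N = 44: power 0.790.

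So 45 is matched exactly. A two-sample t test with d = 0.48 needs 70 per group, so 15 per group does not come from reading 0.48 as d.

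**2. Other routes to 45.** Each needs inputs that the text does not state.
- Repeated-measures interaction, f = 0.24, two measurements, correlation 0.5: λ = 45 × 0.0576 × 2/(1 − 0.5) = 10.368, the same power.
- The same f with three measurements and correlation 0.40.
- Repeated-measures between-groups test, f = 0.48, correlation 0.9.

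The first route does not restore 80% for a standardised mean difference of 0.48. With equal baselines, a post-treatment difference of 0.48 is an interaction f of 0.098 to 0.113, and power at correlation 0.5 is 0.189 to 0.239.

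**3. What f = 0.48 implies.** f is the root mean square deviation of the group means, in SD units.
- Means (0, d, d): f = d√2/3, so d = 0.48/0.4714 = 1.02 SD.
- Means (0, d/2, d): f = d/√6, so d = 0.48/0.4082 = 1.18 SD.

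**4. If 0.48 is a standardised mean difference (assumption), unadjusted, one time point**

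| Comparison | f | Power, N = 45 | Power, N = 54 |
|---|---|---|---|
| Omnibus, means 0, 0.48, 0.48 | 0.226 | 0.239 | 0.284 |
| Omnibus, means 0, 0.24, 0.48 | 0.196 | 0.189 | 0.221 |
| Pairwise t test, d = 0.48 | – | 0.246 | 0.288 |
| Omnibus, means 0, 0.48, 0.72 | 0.30 | 0.39 | 0.47 |
| Omnibus, means 0, 0.48, 0.96 | 0.39 | 0.62 | 0.71 |

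In the first three rows 0.48 is the largest contrast; in the last two a third arm does better still. All mean patterns are assumptions. For 80% omnibus power the first two patterns need 192 and 255 subjects in total.

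**5. Adding baseline adjustment.** The pairwise effect becomes 0.48/√(1 − r²), with 2n − 3 degrees of freedom.

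| Baseline correlation r | Adjusted d | Power, n = 15 | Power, n = 18 |
|---|---|---|---|
| 0.5 | 0.554 | 0.310 | 0.365 |
| 0.7 | 0.672 | 0.427 | 0.499 |
| 0.8 | 0.800 | 0.561 | 0.644 |
| 0.9 | 1.101 | 0.828 | 0.894 |

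**6. VT–RT contrast, whatever the metric of 0.48.** Solving the two-sided t test for 80% power gives a detectable difference of 1.06 SD at 15 per group and 0.96 SD at 18, unadjusted. Baseline adjustment multiplies these by about √(1 − r²):
- r = 0.5: 1.06 × 0.866 = 0.92 and 0.96 × 0.866 = 0.83.
- r = 0.9: 1.06 × 0.436 = 0.46 and 0.96 × 0.436 = 0.42.

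**The case against.** The strongest reply has four parts.

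- **The stated figure reproduces.** There is no arithmetic slip in 45. This stands. A reader might also infer that one-way ANOVA with f = 0.48 is the only possible source of 45; that is not supported, because other G*Power settings give it too. One-way ANOVA is the match that needs nothing beyond the stated inputs.
- **The article never says that 0.48 is a standardised mean difference.** This stands, and the cited meta-analysis is not at hand. A reader might infer that the trial has 20–30% power, or about a one-in-four chance of success. The documents do not support that as a fact: it needs 0.48 to be such a difference, to be the largest contrast, and to be tested without baseline adjustment.
- **The planned mixed model uses repeated measurements, including baseline.** This stands and widens the range, as steps 4 and 5 show. It does not bring back 80% for a pairwise difference of 0.48 unless the baseline correlation is near 0.9, and no correlation is stated.
- **This is a condensed article, and it does not claim power for VT against RT.** The name of the G*Power test may well be in the full protocol, and its absence alone would not be a finding. What remains is that the article asserts a definite power for an effect size whose meaning it leaves open, and that this power does not carry over to a comparison named in the aims.

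**Conclusion.** The concern holds in a conditional form. The 0.80 is correct if 0.48 is Cohen's f for a three-group omnibus test, that is, if the extreme groups differ by about 1.0 to 1.2 SD. The article gives no ground for treating the meta-analytic figure that way.

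If 0.48 is a standardised mean difference and the largest contrast, unadjusted power is 19–25% at 45 and 22–29% at 54. If a third arm does better still, omnibus power is 39–62% at 45 and 47–71% at 54 for the patterns tried. With baseline adjustment, pairwise power at 15 to 18 per group runs from 31–37% (r = 0.5) to 83–89% (r = 0.9). These figures rest on assumed mean patterns and correlations.

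One part does not depend on the metric: an omnibus 80% does not describe the VT–RT comparison, whose unadjusted detectable difference is 1.06 SD at 15 per group and 0.96 SD at 18. The documents do not show that a wrong metric was in fact entered; they show that the stated power cannot be relied on until the metric is known.

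**What to change.** Revise the sample-size paragraph as follows.

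1. State the G*Power test and the effect-size metric actually entered, with any further inputs such as the number of measurements and the correlation.
2. Check which metric and contrast the cited meta-analysis reports for 0.48. If it is a standardised mean difference, convert it and show the assumed pattern of group means.
3. Replace the unqualified 0.80 with achieved power or detectable difference at the fixed 54 subjects, for the omnibus and the VT–RT comparisons, under the planned mixed model with baseline included and over a range of assumed correlations.

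The cost is one paragraph and a less favourable power statement. Recruitment had already closed according to Trial status, and neither enrolment nor conduct changes.
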